**Table 1 T1:**
[figure not shown]
The schedule of enrollment, interventions and assessments.

**Figure 1 F1:**
[figure not shown]
Overview of the study.

### Concomitant care

2.9

Participants who have been taking hypnotic drugs or antidepressants before enrollment will be permitted to continue taking them; however, the addition of hypnotic drugs or treatment other than the given interventions during trial will be prohibited if the participants did not take them before enrollment.

### Data processing and analysis

2.10

#### Data processing

2.10.1

The baseline demographics of the research subjects will be collected by the attending physician through paper-and-pen records at the time of recruitment and will be entered into the database. The data during the treatment and follow-up period will be collected by follow-up staff using the NCDFP, an online telephone survey, which will allow participants to perform this at their convenience. All participants will be reminded throughout the study to fill out the questionnaires during study visits. The follow-up process will be recorded in real time to verify the accuracy of the data. The project manager will be responsible for double checking and exporting the original data from the follow-up system to the required format for data analysis. After the study is completed, the pattern of missing data will be investigated to determine whether the data are completely missing at random or missing non-randomly.^[61]^ Our preliminary analysis will use a robust statistical model, and a sensitivity analysis of nonrandom missing data will be performed if necessary.^[62]^

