In the current research, traditional Chinese Medicine external treatment (TCMET) refers to *Wuqinxi* (also known as five-animal qigong exercise), Chinese medicine massage (*Tuina*), and herbal foot baths, all of which have a long history of use in the treatment of insomnia or depression and will be scheduled in BBT-I to enhance the adherence of the participants. Modern relevant clinical studies have shown the therapeutic effect of *Wuqinxi* on sleep and mental illness.^[25–30]^ Additionally, Chinese medicine massage and herbal foot bath have been reported to improve fatigue,^[31–34]^ and these external therapies have a strong cultural identity in China. Theoretically, primary healthcare institutions in China should be able to perform BBT-I and the above mentioned external traditional Chinese medicine (TCM) treatments. We hypothesize that a combination of BBTI and TCMET improves the adherence and efficacy of behavioral therapy for patients with insomnia in community medical institutions. Additionally, our early exploration found that the loss of follow-up rate was very high in community patients treated only with behavior therapy, and the combination of drugs can effectively ensure the adherence of patients to follow-up. Some clinical and review studies have reported that the antidepressant, trazodone, may have a synergistic effect on CBT-I.^[35–38]^ As Trazodone is legally prescribed by physicians in primary medical institutions in the Chinese community, this trial uses trazodone as a comparator.

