### Implementation procedures

2.8

Once the research candidates have completed several written screening measures, those who meet the inclusion criteria will be screened and evaluated, with the results used as the baseline assessment data. The candidates will be randomly treated in the experimental (i.e., BBT-I combined with TCMET) and control (i.e., BBT-I combined with oral trazodone medication) groups, all of whom must complete the 4 weeks of corresponding treatments. In the first week, the follow-up staff will assist the patient to complete a 1-week sleep diary by telephone, during which, the follow-up staff will provide the necessary guidance and supervision to ensure the participants’ behavioral therapy adherence. After the first week, the participants will be instructed to adjust the behavioral treatment plan. In the second and third weeks, the participants’ behavioral therapy adherence will be followed up with the BBT-I adherence questionnaire, and guidance to ensure behavioral therapy adherence will be given during the follow-up. At the end of the fourth week, sleep and mood-related scales will be evaluated, and the BBI-I adherence questionnaire will be performed again. Participants who demonstrate an improvement will continue maintenance therapy, and participants with no improvement over the 4-week study period will have their treatment plan adjusted or will be recommended to be referred to a higher-level hospital. During the treatment period, the treatment will be discontinued in participants who cannot cooperate with the treatment due to disease or other reasons.

Three months after the end of the 4-week treatment, a telephone follow-up will be performed to evaluate the therapeutic efficacy. All follow-up tasks above will be conducted through the network chronic disease follow-up platform (NCDFP) developed by Jiangsu Vocational College of Medicine (Jiangsu Province, China), and will be completed by trained students through the telephone interview. Table 1 shows the participant timeline, and Figure 1 provides an overview of the study.

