Analysis of therapeutic efficacy within and between groups, and adherence analysis between the groups: the measurement data will be presented as the mean ± standard deviation, and the statistical inference will be performed using the *t*-test and rank-sum test. The count data will be presented as frequency (composition ratio), and Chi-Squared analysis or nonparametric analysis will be performed for exact probability or statistical inference, respectively. Sensitivity analyses will be used to assess the impact of missing outcomes, which include worst case assumptions and/or multiple imputation methods. Subgroup analysis will be used to analyze the main outcome and adherence according to associated medication (Trazodone used or not) and education level of the research subjects. SPSS 21.0 software (IBM, Armonk, NY) will be used for statistical analysis, which will adopt two-sided tests. *P* ≤ .05 will be considered to indicate statistically significant differences in the test.

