#### Sample size calculation

2.10.3

The main observation index of this study is the ISI, and the sample size is calculated based on the two independent sample *t*-test. The sample size adjustment is based on the pool variance.^[63]^ According to our previous reports,^[25,50]^ the mean effect size of the control group is 8.4. A mean effect size difference (δ) of an increase in 2.5 for the experimental group relative to the control group will be considered effective. The overall sample standard deviation of ISI in the previous study was 4.1.^[49]^ Assuming that the variances of the 2 groups are similar, in a two-sided test with α at .05, sample size ratio of the 2 groups at 1:1, the test power (1 − β) at 80%, the sample size is calculated to be 88. We anticipate 10% loss to follow-up or drop-off rate. Thus, t total sample size is calculated as 96.8, which is approximately 98 people, including 49 people in each of the 2 groups.

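### Section 2.10.1 ties missing data to an unidentified robust model, while 2.10.2 names only observed-value tests for the ISI and adherence scores, so it is unclear which analysis decides

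*Protocol article*

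**What the plan says.** Section 2.10.1 (Data processing) plans to examine the pattern of missing data and continues: "Our preliminary analysis will use a robust statistical model". The same sentence adds a sensitivity analysis for nonrandom missingness, to be done only where it is thought necessary. The model is not identified there or anywhere else in the article.

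Section 2.10.2 (Data analysis) covers efficacy and adherence. For measurement data, "the statistical inference will be performed using the *t*-test and rank-sum test". For count data, "Chi-Squared analysis or nonparametric analysis will be performed for exact probability or statistical inference, respectively". On missing outcomes it adds: "Sensitivity analyses will be used to assess the impact of missing outcomes, which include worst case assumptions and/or multiple imputation methods".

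Section 2.10.3 sizes the trial on a two-sample t-test of the ISI, needing 88 participants, and raises this to 98: "We anticipate 10% loss to follow-up or drop-off rate".

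The data available are as follows. The ISI is measured at baseline, week 4 and 3 months after treatment (2.4.1). In weeks 2 and 3 "behavioral therapy adherence will be followed up with the BBT-I adherence questionnaire", and the questionnaire is repeated at week 4 (2.8). On retention, section 1.1 reports from the group's early experience that "the loss of follow-up rate was very high in community patients treated only with behavior therapy", and that adding drugs helped to keep patients in follow-up.

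**The concern.** The two analysis sections do not describe the same inference. One links missing data to a model. The other names no model for continuous outcomes, only two tests that drop anyone without the value being tested. The word preliminary makes it worse, because it could mean primary or an early look. Two analyses could each be reported as the main one, and they can differ exactly when loss is informative.

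Adherence is the stated objective (1.2) and sits with the ISI under the main outcome (2.4.1). If low adherers tend to leave before week 4, and more do so in one arm, those who remain are no longer comparable and a week-4 t-test inherits the imbalance. Adherence scores from weeks 2 and 3 could largely correct this where they exist, but no primary analysis that uses them for this purpose is named.

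**Working it through.** **1. The plan's own figure.** Inputs from 2.10.3: difference 2.5, SD 4.1, two-sided α 0.05, power 80%, ratio 1:1.
- Normal approximation: n per arm = 2 × (1.960 + 0.842)² × (4.1/2.5)² = 2 × 7.849 × 2.690 = 42.2, so 43 per arm and 86 in total.
- With the t distribution: 43.2, so 44 per arm and 88 in total. The stated 88 reproduces.
- Inflation: 88 × 1.1 = 96.8 as stated; 88/0.9 = 97.8, so 98. Either way the final 98 is sound.

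**2. How many fall out.** 98 × 0.9 = 88.2, so about 10 of 98 have no value at the planned loss. A t or rank-sum test without imputation omits them. Precision is already paid for: t-test power is 80.7% at 44 per arm, against 84.8% at 49. The issue is comparability and which result counts, not power.

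**3. Size of the possible bias, adherence at week 4.** The document gives no loss by arm and no correlations, so these are assumptions: 49 per arm, no true difference, three equally correlated normal weekly scores (correlation 0.5 to 0.7), and dropout after week 3 sampled with weight exp(−k × mean standardised week 2–3 score). The main setting, with k = 1.5 and unequal loss, used 4,000 simulated trials per setting. The equal-loss and weak-selection checks used 3,000.

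| Loss, arm A vs arm B | Selection k | Bias of week-4 t-test (SD) | Rejection under no difference |
|---|---|---|---|
| 10% vs 10% | 1.5 | under 0.01 | about 5.6% |
| 5% vs 15% | 0.5 | about 0.04 | 4.8–5.4% |
| 5% vs 15% | 1.5 | 0.06–0.09 | about 7–9% |
| 5% vs 25% | 1.5 | 0.14–0.19 | 11–16% |

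The Monte Carlo standard error at a 5% rate with 3,000 trials is √(0.05 × 0.95/3000) = 0.4 percentage points, so 5.6% is within noise of nominal. The last row implies (5 + 25)/2 = 15% overall loss, which is above the plan.

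At k = 1.5 with unequal loss, an estimate that regresses week 4 on weeks 2 and 3 within each arm left bias of 0.01 SD or less. It stands in for a likelihood-based model. It works here because loss was made to depend only on scores that were recorded.

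**4. Why the choice of primary analysis matters for the ISI.** Take the planning means, 8.4 and 8.4 + 2.5 = 10.9, for those observed, and suppose 10 lost participants count as zero change. This is an extreme assumption for illustration, not a forecast.
- Split 5/5 (experimental/control): (44/49) × 10.9 − (44/49) × 8.4 = 2.24.
- Split 7/3: (42/49) × 10.9 − (46/49) × 8.4 = 1.46.
- Split 10/0: (39/49) × 10.9 − 8.4 = 0.28.

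The observed-value comparison gives 2.5 in all three. No simulation of ISI bias was run.

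**The case against.** The strongest reply is that this is one loose clause in a data-processing paragraph of a condensed article. The trial calls itself exploratory (1.3), a fuller protocol or analysis plan may name the model, and both sections already answer missing data with sensitivity analyses. Much of that stands. Leaving the model's details to another document is no fault, and choosing a mixed model over multiple imputation is partly preference. What remains is that the article's own two sections point to different analyses, and further detail cannot make both the deciding one.

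A reader might infer more than the text supports:
- *That all inference rests on t and rank-sum tests.* It does not. Section 2.10.2 also names chi-squared or exact methods for count data, and the point here is confined to continuous outcomes.
- *That lost participants are ignored.* They are not. Worst-case and/or multiple-imputation analyses bring them back, and imputation could use the week 2–3 scores. These analyses are secondary, with the choice between them left open.
- *That 88 is a declared completer set.* It is the number required before inflation. Complete-case use is inferred from the tests named.
- *That the protocol predicts unequal loss.* Section 1.1 describes patients given behavioural therapy alone, and neither randomised arm is that. Only controls who refuse trazodone receive it (2.7), and nothing is said about loss under the TCM treatments. Unequal loss is plausible, but its direction is unknown.
- *That bias is expected at 10% loss.* It needs unequal loss and strong selection together.

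**Conclusion.** The point holds as an inconsistency about the deciding analysis. Section 2.10.1 promises an unidentified robust model, and 2.10.2 names only observed-value tests for the ISI and adherence scores. As written, about 10 of 98 would be absent from the main comparison and return only in sensitivity analyses.

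The harm is conditional. It ranges from negligible (equal 10% loss, or weak selection) to about 0.06 to 0.09 SD with rejection near 7 to 9% (5% versus 15% loss, strong selection), and is larger if loss exceeds the plan and is uneven. Those figures concern week-4 adherence and rest on assumed loss by arm, correlation and selection strength. It is worth correcting because the remedy is cheap and the adherence comparison is the trial's objective. It does not show that the trial's result will be biased.

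**What to change.** In 2.10.2 name one primary analysis, by allocated arm, that uses all recorded values. Align 2.10.1 with it, replacing the word preliminary with primary or deleting it.

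- **Adherence:** a repeated-measures mixed model of the questionnaire total at weeks 2, 3 and 4, with arm, occasion and arm-by-occasion, and the week-4 contrast as the deciding one. A participant with no adherence score at all still contributes nothing to it.
- **ISI:** a mixed model of baseline, week 4 and 3 months, with baseline in the outcome vector and a common baseline mean across arms. Baseline has to be included: a model of week 4 and 3 months alone recovers nothing for someone who leaves before week 4 and is not reached later. Including it also adds precision.
- **Acceptable alternative:** multiple imputation as the primary analysis, using baseline ISI and week 2–3 adherence.
- **Keep** the t and rank-sum tests as supportive, and worst-case or other nonrandom-missingness analyses as sensitivity.

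The cost is wording in two sections and slightly more analysis work. The planned software covers it through SPSS MIXED. No new data and no change in sample size are needed. With 25 of 98 enrolled at the article's status date, the change could be made early.

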#### Data analysis

2.10.2

Analysis of the validity and reliability of the BBT-I adherence questionnaire: the adherence reliability of the behavioral therapy will evaluate the internal consistency of the behavioral therapy adherence through the standard Cronbach's α coefficient and the total correlation coefficient of the item. Convergence validity analysis will be based on the participants’ 1-week daily sleep diary, which will be compared with the consistency of the questions answered in the BBT-I adherence questionnaire to observe whether the questionnaire truly reflects the accuracy of the patient's adherence with various behavioral treatments. For example, for the question “Can you get up on time in the morning in the last week?” if the patient's answer is “accomplish less than half the time” then the patient should have gotten up on time 1 to 3 days during the last week; if the patient's answer is “accomplish more than half the time,” the sleep dairy of this patient should indicate that he or she has gotten up on time for 4 to 6 days in the last week; if the patient's answer is “not able to accomplish,” the sleep dairy of this patient should indicate that he or she had 0 days getting up on time in the last week; if the patient's answer is “accomplish most of the time,” the sleep diary of this patient should indicate that he or she has gotten up on time for all 7 days in the last week. Waking up on time is defined as getting up no more than 15 minutes before or after the agreed time to get up. Failure to meet the above criteria will be considered inconsistency between questionnaire's answer and the sleep diary. Lastly, the consistency ratio will be determined, and the correlation coefficient will be calculated.

Analysis of therapeutic efficacy within and between groups, and adherence analysis between the groups: the measurement data will be presented as the mean ± standard deviation, and the statistical inference will be performed using the *t*-test and rank-sum test. The count data will be presented as frequency (composition ratio), and Chi-Squared analysis or nonparametric analysis will be performed for exact probability or statistical inference, respectively. Sensitivity analyses will be used to assess the impact of missing outcomes, which include worst case assumptions and/or multiple imputation methods. Subgroup analysis will be used to analyze the main outcome and adherence according to associated medication (Trazodone used or not) and education level of the research subjects. SPSS 21.0 software (IBM, Armonk, NY) will be used for statistical analysis, which will adopt two-sided tests. *P* ≤ .05 will be considered to indicate statistically significant differences in the test.

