#### Sleep diary

2.3.2

The sleep diary based on the web-based follow-up system will be used to obtain subjective estimates of sleep and wake-up time of the participants daily. Each participant will be asked to cooperate with the follow-up staff to report the information about their sleep the night before, including bedtime, sleep onset latency, number and duration of night-time awakenings, last awakening time, wake-up time, subjective evaluation of sleep quality, and use of sleep aid drugs. A 1-week sleep diary will be obtained in the first week after the study enrollment. During the telephone follow-up, the follow-up staff will give necessary guidance and supervision to ensure the patient's adherence to behavioral therapy.

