#### BBT-I adherence questionnaire

2.3.3

Good adherence to therapy is key to the curative effect of behavioral therapy.^[46]^ One of the main hypotheses of this study is that both the external TCM and trazodone can help patients to improve their therapeutic adherence. Unfortunately, there are currently few relevant studies and no gold standard for evaluating adherence with CBT-I or its brief model.^[22,47,48]^ To evaluate the adherence of participants, our team devised the BBT-I adherence questionnaire based on the contents of sleep restriction and stimulus control, which focuses on the patient's behavioral therapy adherence in the past week, including insistence on not going to bed at night without sleeping, getting up early in the morning, not going to bed during the day, not staying in bed at night after attempting to sleep for 30 minutes, and not doing anything unrelated to sleep or having sex (especially using cell phone and thinking). Each content will be scored from 0 to 3 as follows: score 0, difficult to accomplish; score 1, accomplish less than half the time; score 2, accomplish more than half the time; score 3, accomplish most of the time.

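### The diary check of the adherence questionnaire needs both to cover the same week, but the text schedules the diary in week 1 and the questionnaire in weeks 2, 3 and 4 without fixing a matching pair

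*Protocol article*

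**What the plan says.** The relevant statements are spread over five sections of the protocol article.

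- **Diary timing.** Section 2.3.2: "A 1-week sleep diary will be obtained in the first week after the study enrollment". Section 2.8 agrees: "In the first week, the follow-up staff will assist the patient to complete a 1-week sleep diary by telephone". No section schedules a later diary.
- **Questionnaire timing.** Section 2.8: "In the second and third weeks, the participants’ behavioral therapy adherence will be followed up with the BBT-I adherence questionnaire", and then "At the end of the fourth week, sleep and mood-related scales will be evaluated, and the BBI-I adherence questionnaire will be performed again". No week-1 administration is stated, and the call day within weeks 2 and 3 is not given.
- **Recall period.** Section 2.3.3 says the questionnaire concerns "behavioral therapy adherence in the past week".
- **Change of plan.** Under section 2.7, the recommended bedtime and wake-up time are revised from the one-week diary. Section 2.8 puts the adjustment of the plan after the first week.
- **Validation rule.** Section 2.10.2 takes as comparator the "1-week daily sleep diary, which will be compared with the consistency of the questions answered in the BBT-I adherence questionnaire". In its worked example, the four answers correspond to 0, 1 to 3, 4 to 6 and 7 diary days of getting up on time in the last week. On time means within 15 minutes of the agreed time. Any other combination counts as an inconsistency. A consistency ratio and a correlation coefficient follow.

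**The concern.** The matching rule treats a diary count and a questionnaire answer as two readings of the same seven days. If they come from different weeks, a participant who answers truthfully can be scored as inconsistent because behavior changed, and an inaccurate answer can be scored as consistent by chance. Change is to be expected: the plan is adjusted after week 1, and staff give adherence guidance during both the diary calls and the later questionnaire calls.

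The check matters because improving adherence is the stated objective (1.2), the questionnaire is listed under the main outcome indicator (2.4.1), and section 2.3.3 acknowledges that there is no gold standard. The diary comparison is the only planned check of the answers against another record. Section 4 presents it as one of the study's innovations. The problem is also one of data collection: if no same-week pair is collected, no later analysis plan can create one.

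**Working it through.** The plan gives no figure to reproduce here. The check is a count of shared days, followed by a comparison of the contents of the two instruments.

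**1. Shared days.** Inputs: the diary covers days 1 to 7 (2.3.2, 2.8); the questionnaire looks back 7 days (2.3.3); call day d lies in days 8–14 (week 2) or 15–21 (week 3), or is day 28 (end of week 4) (2.8). The text does not say whether the look-back includes the call day, so both conventions are counted:

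- look-back is the 7 days before the call (d−7 to d−1): shared days = max(0, 15 − d) for d ≥ 8;
- look-back is the 7 days ending on the call day (d−6 to d): shared days = max(0, 14 − d) for d ≥ 8.

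| Administration | 7 days before the call | 7 days ending on the call day |
|---|---|---|
| Week 2, day 8 | 15 − 8 = 7 | 14 − 8 = 6 |
| Week 2, day 11 | 15 − 11 = 4 | 14 − 11 = 3 |
| Week 2, day 14 | 15 − 14 = 1 | 14 − 14 = 0 |
| Week 3, any day 15–21 | 0 | 0 |
| End of week 4, day 28 | 0 | 0 |

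Two of the three administrations share no day with the diary under either convention. The week-2 one shares all seven only on day 8, and only if the look-back is the seven days before the call.

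**2. Effect on the scoring rule.** Suppose a participant got up on time on 3 days in the diary week and on 4 days in the later week being recalled. The truthful answer falls in the 4-to-6 band, the diary falls in the 1-to-3 band, and the pair is scored inconsistent. A real change of one day is enough when it crosses a band edge.

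**3. Effect of the changed agreed time.** The on-time window is ±15 minutes. If the agreed get-up time moves by more than 15 + 15 = 30 minutes after week 1, the old and new windows do not overlap. A participant who keeps the same get-up time then cannot be on time under both plans. The article gives no size for the adjustment, so this only shows how the reference can change.

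**4. Item coverage (secondary).** The diary fields named in section 2.3.2 are "bedtime, sleep onset latency, number and duration of night-time awakenings, last awakening time, wake-up time, subjective evaluation of sleep quality" and use of sleep aids. Against the five contents of the questionnaire (2.3.3):

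| Questionnaire content | Directly matching listed field |
|---|---|
| Not going to bed until sleepy | Bedtime |
| Getting up in the morning as agreed | Wake-up time |
| No bed use in the day | None listed |
| Leaving bed after 30 minutes awake | None listed; sleep latency and awakenings can point to nights when the rule applied, but not whether the participant got up |
| No unrelated activity in bed | None listed |

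**The case against.** The strongest reply is that a valid pair may be intended. The matching rule speaks of the last week throughout. A call at the very start of week 2 would look back on the diary week, and section 2.8 has participants instructed on adjusting the plan after the first week, so a contact near day 8 is plausible. At such a call the recalled get-up time would still be the week-1 time. Table 1, the assessment schedule, is not visible and could fix that day or add an administration. This stands. A reader might infer that none of the three questionnaires can match the diary, or that the agreed times must differ in every pair; the documents do not support either for week 2. They do not, however, fix the day or name the pair, and nothing in this reply rescues weeks 3 and 4.

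A reader might also infer that exactly two of the five questionnaire contents can be checked. That goes too far. The diary fields are introduced by the word *including*, so the list may be incomplete, and the form itself is not shown.

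Nor is the diary check the questionnaire's only support: section 2.10.2 also plans Cronbach's α and item-total correlations. Those describe internal consistency, though, and do not show whether answers reflect behavior.

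Finally, the between-group adherence comparison does not use the consistency ratio, and the sample size rests on the ISI. The efficacy analysis is therefore untouched. What is affected is the evidence that the adherence score measures adherence.

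**Conclusion.** The concern holds in a limited form. As the text stands, the convergent-validity check needs the same seven days and the same agreed times, and the schedule does not secure either. Weeks 3 and 4 have 0 of 7 days in common with the diary. Week 2 has between 7 and 1, or between 6 and 0, depending on the look-back convention and on a call day that is not stated.

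Disagreement from unmatched pairs would mix real change and coaching with questionnaire error. It would be wrong to attribute it wholly to either. Agreement from such pairs would be equally hard to interpret.

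This conclusion assumes that the diary is kept in week 1 only and that Table 1 adds no matching administration. If Table 1 does fix a same-week pair, what remains is to say so in section 2.10.2. The item-coverage point is conditional on the full diary form. This should be corrected, but it does not threaten the ISI analysis.

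**What to change.** 1. Give the questionnaire also at the last diary call of week 1. Alternatively, fix the week-2 call on day 8, before the plan is adjusted, and define the look-back as the seven days before the call.
2. State in section 2.10.2 that only this pair enters the consistency ratio and the correlation, judged against the times agreed for week 1. Later administrations serve the adherence comparison, not the validation.
3. Leave participants already past week 1 without such a pair out of the validation set. Section 5 reports 25 of 98 enrolled on 17 April 2021. If none of those 25 had a pair, up to 98 − 25 = 73 could still contribute, before any loss to follow-up and fewer if enrollment has since moved on.
4. Check whether the full diary form records daytime bed use, leaving bed after 30 minutes awake, and activity in bed. If it does not, limit the validity claim to the items that the diary can check.

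The cost is a few questions on a call that already takes place and a slightly smaller validation sample. No treatment and no efficacy analysis changes.

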#### Main outcome indicator

2.4.1

The ISI will be used to evaluate the improvement of insomnia at the baseline level before the treatment, at the end of the 4-week treatment period, and 3 months after the end of treatment. A reduction in the ISI score of ≥8 points is considered effective, and an ISI score ≤8 is considered cured.^[49,50]^ The BBT-I adherence questionnaire will be used to evaluate the efficacy of TCMET or trazodone on the adherence of BBT-I.

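### ISI is to be compared between arms with unadjusted tests although every participant has a baseline ISI; adjusting for it gains precision at no cost, and the protocol should say what its SD of 4.1 measures

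*Protocol article*

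**What the plan says.** Protocol article, section 2.10.2 (Data analysis): for measurement data, within and between groups, "statistical inference will be performed using the *t*-test and rank-sum test". No covariate is named. The text does not say whether the between-group test is applied to follow-up scores or to changes from baseline.

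Section 2.4.1 (Main outcome indicator): ISI is assessed "at the baseline level before the treatment, at the end of the 4-week treatment period, and 3 months after the end of treatment". Section 2.2.1 requires an ISI total above 10 for entry, and section 2.8 uses the screening results as baseline data, so each randomized participant should have a baseline value.

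Section 2.10.3 (Sample size calculation): "The main observation index of this study is the ISI, and the sample size is calculated based on the two independent sample *t*-test". Its inputs are that "the mean effect size of the control group is 8.4", that "A mean effect size difference (δ) of an increase in 2.5 for the experimental group relative to the control group will be considered effective", and that "The overall sample standard deviation of ISI in the previous study was 4.1". The result: "the test power (1 − β) at 80%, the sample size is calculated to be 88". The total becomes 98 after a 10% allowance for loss.

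Section 2.6 (Randomization) specifies complete randomization and describes no stratification.

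**The concern.** Two features of the plan belong together.

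First, the named tests ignore baseline ISI. In a trial of 49 per arm with unrestricted randomization, the arms can differ in baseline ISI by chance by an amount that is not small beside the target difference of 2.5. Neither a test of follow-up scores nor a test of changes adjusts for this properly. Baseline ISI would normally predict later ISI, and an analysis that uses it gives a narrower confidence interval from the same patients.

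Second, the sizing appears to mix two scales. Lower ISI is better and section 2.4.1 counts a reduction as success, so a control effect of 8.4 with a further increase of 2.5 counted as better reads sensibly only as improvement from baseline. The SD of 4.1, however, is described as the SD of ISI, and it carries a different citation from the 8.4. The SD of a change and the SD of a score coincide only at a correlation of 0.5 (equal SDs at both times).

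At stake are precision, and how far the 80% power can be relied on once the analysis variable is settled.

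**Working it through.** **Inputs.** From section 2.10.3: difference δ = 2.5, SD 4.1, two-sided α = 0.05, 1:1 allocation, 80% power, 10% loss. Assumed, because the protocol does not give them: the baseline/follow-up correlation r, and (except where stated) SD 4.1 at both times.

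**Reproducing the plan's figure.** Two-sample t-test, noncentral t with noncentrality δ / (SD × √(2/n)):
- n = 44 per arm: 2.5 / (4.1 × √(2/44)) = 2.5 / 0.874 = 2.86, power 80.7%. With 43 per arm, power is 79.8%.
- So 44 per arm, 88 in total, as stated. 88 × 1.10 = 96.8 and 88 / 0.90 = 97.8; either leads to 98.

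The arithmetic is correct.

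**Three analyses of the same 88 patients.**
- Follow-up scores, unadjusted: SD = 4.1.
- Change scores, unadjusted: SD = 4.1 × √(2(1 − r)).
- Follow-up score adjusted for baseline (ANCOVA): residual SD = 4.1 × √(1 − r²), with one degree of freedom fewer.

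| r (assumed) | Follow-up t-test | Change SD | Change t-test | ANCOVA SD | ANCOVA |
|---|---|---|---|---|---|
| 0.3 | 80.7% | 4.85 | 66.6% | 3.91 | 84.2% |
| 0.4 | 80.7% | 4.49 | 73.3% | 3.76 | 87.0% |
| 0.5 | 80.7% | 4.10 | 80.7% | 3.55 | 90.4% |
| 0.6 | 80.7% | 3.67 | 88.5% | 3.28 | 94.2% |
| 0.7 | 80.7% | 3.18 | 95.5% | 2.93 | 97.7% |

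A change-score test would need 122 evaluable patients at r = 0.3 and 104 at r = 0.4 for 80% power. ANCOVA would need 80 at r = 0.3, 66 at r = 0.5 and 46 at r = 0.7.

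**Chance imbalance.** With SD 4.1 and 49 per arm, the difference in baseline means has standard error 4.1 × √(2/49) = 0.83, so a 95% range of about ±1.6 points, some 65% of δ (1.62 / 2.5). At r = 0.5 an imbalance of 1.62 moves the follow-up comparison by 0.5 × 1.62 = 0.8 points and the change comparison by the same amount in the opposite direction. ANCOVA removes this shift.

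**What if 4.1 is not the follow-up SD?** If it is a baseline SD and the follow-up spread is larger (assumed values, 44 per arm):
- Follow-up SD 5.0: unadjusted 64.0%; ANCOVA 68.1% at r = 0.3 and 76.3% at r = 0.5; r of about 0.57 is needed for 80%.
- Follow-up SD 6.0: unadjusted 48.9%; ANCOVA 52.6% and 60.7%; r of about 0.73 is needed.

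If 4.1 is really the SD of the change (equal score SDs at both times), the change-score test has 80.7% and ANCOVA has 93.9%, 90.4% and 86.6% at r = 0.3, 0.5 and 0.7. An unadjusted follow-up test then has 91.7%, 80.7% and 59.1%.

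**The case against.** The strongest reply is that nothing here is an error. An unadjusted two-sample test is valid under randomization, and its type I error already allows for chance imbalance. Sizing and analysis both rest on the t-test, and the trial calls itself exploratory. All of that stands: the loss is of precision, and the comparison is not systematically biased.

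A reader might infer from the mixed scales that 88 is too few. The documents do not support that. They nowhere say that changes will be tested. Under randomization the expected arm difference in change equals that in follow-up score, so δ = 2.5 with a score SD is coherent for a follow-up-score test. With 4.1 as the score SD at both times, power falls short only if changes are tested and r is below 0.5; above 0.5 the plan is conservative. Reading the effect as a change is itself an inference, though a strong one.

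A reader might also infer that ANCOVA settles both matters and protects 80% at any correlation. It does not. If 4.1 is a score SD, that protection requires it to be the follow-up one, and the time point is not given. The entry threshold of ISI above 10 truncates the baseline distribution, which makes equal SDs a questionable assumption. For the same reason the protocol should not be told to declare 4.1 a score SD, or to attribute its 80% to an adjusted analysis: it was computed for an unadjusted test.

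Finally, covariates are often left to an analysis plan. Here, though, the article names its tests and sizes on one of them. The robust model that section 2.10.1 mentions for a preliminary analysis is unspecified and names no covariate. Improving on a stated method is a fair comment.

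**Conclusion.** The point holds as a free improvement to a valid analysis, with a request to clarify one input. At 44 per arm, δ = 2.5 and SD 4.1 at both times, adjusting for baseline raises power over the follow-up-score test by 3.5 percentage points at r = 0.3 (84.2 − 80.7), 9.7 at r = 0.5 and 17.0 at r = 0.7. Against a change-score test the gains are 17.6, 9.7 and 2.2 points. These sizes rest on an assumed r and on equal SDs; neither is in the protocol. The stated 88 and 98 are not shown to be wrong. Whether 80% is actually secured, with or without adjustment, cannot be judged until the sponsor says what 4.1 measures.

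**What to change.** In section 2.10.2, make the main ISI analysis a linear model of follow-up ISI on treatment arm and baseline ISI, reporting the adjusted mean difference with its 95% CI. Analyze the Pittsburgh sleep quality index and the Zung anxiety and depression scales in the same way, each with its own baseline. Keep the t-test and rank-sum test as supportive.

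In section 2.10.3, state from the cited source whether 4.1 is the SD of a baseline score, a follow-up score or a change, and at which time point. Say whether 8.4 and 2.5 are changes from baseline. If the power of the adjusted analysis is quoted, give the assumed correlation and follow-up SD beside it.

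The cost is wording plus one degree of freedom per model. No patients, visits or measurements are added, and participants already enrolled are unaffected.
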